### Study design

## *Approach*

Children enrolled in the study as described under Aim I in chapter 3, may participate in the follow up study if they tested positive for *M. pneumoniae* by either real time PCR or culture in a sample taken during the first visit. The results of the tests taken during the first visit will be made available to parents and participants about one week prior to the second visit. Subsequently they will be asked to participate in the following protocol

*Definitions*

1. Children with RTI in combination with the presence of *M. pneumoniae,* as detected by either culture or real-time PCR in either the oropharyngeal swab or the nasopharyngeal lavage taken during the first visit, i.e. **group A+** or **group HAP+**. (Note: these children not necessarily suffer from disease caused by infection with *M. pneumoniae*. The gold standard for *M. pneumoniae* infection in this study is serology in combination with standard PCR.)

2. Healthy children tested positive for *M. pneumoniae* by culture or real-time PCR in either the oropharyngeal swab or the nasopharyngeal lavage taken during the first visit, i.e. **group B+**.

*Follow up protocol*

In the follow up protocol participants will be tested for the presence of *M. pneumoniae* in the nasopharynx and oropharynx once a month during a maximum period of one year or until they test negative in both tests (culture and real-time PCR) on two successive occasions. For monthly sample collections, either house-calls will be performed or participants may visit the emergency department of the Erasmus MC – Sophia, whichever is most convenient for participants at that time. If a child, participating in this study, suffers from a RTI during the follow up period, he/she will be evaluated, during daytime, by a physician specialized in pediatric infectious diseases. At all times during the follow up study, parents are free to take him/her to their own general practitioner. For emergencies parents should follow the normal procedures.

*Clinical samples*

Each month a nasopharyngeal lavage and an oropharyngeal swab will be taken and real-time PCR and culture will be performed for *M. pneumoniae* as described previously in chapter 3. Test results will be made available to the participants and their parents every month since these results determine whether the study is continued for each participant individually.

*Clinical data*

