## *Inclusion criteria*

Group A+/HAP+

Eligible for group A/HAP

Real-time PCR or culture positive for *M. pneumoniae*

Written informed consent for receiving results of the *M. pneumoniae* tests.

Written informed consent for group A/HAP and A+/HAP+

Group B+

Eligible for group B

Real-time PCR or culture positive for *M. pneumoniae*

Written informed consent for receiving results of the *M. pneumoniae* tests.

Written informed consent for group B and B+

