## *Exclusion criteria*

Group A+/HAP+

Non-eligible for group A/HAP

Real time PCR or culture negative for *M. pneumoniae*

No written informed consent for receiving results of the *M. pneumoniae* tests.

No written informed consent for group A+/HAP+

Group B+

Not eligible for group B

Real time PCR or culture negative for *M. pneumoniae*

No written informed consent for receiving results of the *M. pneumoniae* tests.

No written informed consent for group B+

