### Study Methods

*Additional visits for follow up*

Group A+/HAP+ and B+ will be asked to return for a maximum of 12 follow-up visits after visit 1. For convenience of participants, house calls will be offered to each participant and their parents and performed by the research team. During these visits a nasopharyngeal lavage and an oropharyngeal swab will be taken and there will be additional short questionnaires.

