### Statistics

*Research question(s)*

Does the presence of *M. pneumoniae* in healthy individuals at a certain time point reflect a persistent carriage stage or merely an increasing or declining bacterial load before or after an infection?

*Analysis*

Bacterial load will be determined in samples taken from each visit. These will be used mainly in a descriptive fashion. We hypothesize that a persistent carriage stage does not exist and expect to find clearance of bacteria in all patients eventually. The number of RTI will be scored in each group. The time to clear all bacteria (defined by a negative PCR) will be determined for each individual and means will be compared between each group. The genotype of *M. pneumoniae* will be determined in every sample to compare to ‘time to clear’ and severity of infections.

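### Ancillary carriage study: mean time to clear has no value for children not seen to clear, clearance is looser than the follow-up rule, and the exclusion wording contradicts the inclusion

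*Protocol*

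**What the plan says.** The ancillary study asks whether a positive test in a healthy child reflects persistent carriage, or a load rising or falling around an infection (Protocol 12.1.6). The stated expectation is: "We hypothesize that a persistent carriage stage does not exist and expect to find clearance of bacteria in all patients eventually".

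- **Analysis (12.1.6).** "The time to clear all bacteria (defined by a negative PCR") "will be determined for each individual and means will be compared between each group". Load at each visit is also reported, mainly descriptively.
- **Length of follow-up (12.1.3 and 12.1.5).** Children are tested "once a month during a maximum period of one year" and "will be asked to return for a maximum of 12 follow-up visits after visit 1". Section 7.3 lets a subject leave at any time.
- **When follow-up may end earlier (12.1.3).** Testing goes on "until they test negative in both tests (culture and real-time PCR) on two successive occasions".
- **Eligibility (12.1.4).** Inclusion: "Real-time PCR or culture positive for" *M. pneumoniae*. Exclusion: "Real time PCR or culture negative for" *M. pneumoniae*. Section 12.1.3 admits a child positive on either test. The sample size paragraph of 12.1.4 treats PCR positivity alone as making a child eligible and expects 50 such children.

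**The concern.** Three pieces of wording do not fit together.

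1. Time to clear is right-censored, because follow-up is capped and children can leave. It cannot be determined for every child. A mean needs a number from each child, so those not seen to clear must be left out or given an arbitrary value. If they are left out, the summary ignores the children who bear most directly on the research question.
2. The analysis accepts a negative PCR as clearance, whereas the design does not treat one negative as enough to stop testing. A carrier missed once by PCR could be given a clearance time even though the confirming visits are collected.
3. A PCR-positive, culture-negative child meets both the inclusion and the exclusion criterion. This concerns who is enrolled and is separate from the first two items.

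At stake are the reported duration of carriage in each group and the comparison between groups.

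**Working it through.** **The plan's own figure.** 10% of the half of the main study still to be enrolled: 0.10 × (500 + 500)/2 = 50. This matches the stated 50. The ancillary study states no power or effect size to check.

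**Inputs.** The cap of 12 monthly visits comes from the protocol. The clearance rate, persistent fraction, monthly loss, detection probability per visit and independence between visits are assumptions; the documents give none of them.

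**A. Mean of observed times.** Let a fraction π never clear and let the rest clear exponentially with mean m months. Clearance is recorded at the next monthly visit k, with p_k = exp(−(k−1)/m) − exp(−k/m), k = 1 to 12.

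- Mean among children seen to clear: Σ k(1−π)p_k / Σ (1−π)p_k. The factor (1−π) cancels, so with perfect detection this mean does not depend on π.
- 12-month restricted mean on the same visit scale: Σ k(1−π)p_k + 12 × (proportion uncleared).

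| m (months) | Mean of observed times, any π | Restricted mean, π = 0 | Restricted mean, π = 40% |
|---|---|---|---|
| 1.5 | 2.05 | 2.05 | 6.03 |
| 2 | 2.51 | 2.54 | 6.32 |
| 3 | 3.30 | 3.46 | 6.88 |
| 6 | 4.64 | 5.63 | 8.18 |

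At m = 6, 13.5% are uncleared at 12 months even with no persistent carriers.

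**B. One worked scenario.** Median clearance 2.5 months, so m = 2.5/ln 2 = 3.61, with π = 10%.

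- Restricted mean of the true clearance time: 0.9 × 3.61 × (1 − exp(−12/3.61)) + 0.1 × 12 = 3.13 + 1.20 = 4.33 months.
- Mean of observed times, perfect detection and no loss: 3.68 months. Rounding up to the next visit inflates this figure, so the comparison with 4.33 is lenient to the plan. On the visit scale the restricted mean is 0.868 × 3.68 + 0.132 × 12 = 4.78.
- Mean of first-negative times, 85% detection and 3% monthly loss: 2.77 months.

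A gap of about 0.6 months therefore remains with perfect detection and no loss (4.33 − 3.68 = 0.65). In the less favourable case it is about 1.6 months (4.33 − 2.77 = 1.56).

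**C. One negative against two in succession.** For a child who carries throughout, with detection probability s at each of 12 independent visits:

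- At least one negative: 1 − s^12.
- Two successive negatives: start with a = 1, b = c = 0 and at each visit replace a by (a+b)s, b by a(1−s) and c by c + b(1−s). After 12 visits, c is the answer.

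| Detection s | At least one negative PCR | Two successive negative PCRs |
|---|---|---|
| 95% | 46% | 2.6% |
| 90% | 72% | 9.7% |
| 85% | 86% | 20% |

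The last column uses PCR alone. Requiring culture to be negative as well can only lower it.

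**D. Eligibility, side by side.** Take a child who is PCR-positive and culture-negative. Section 12.1.3 admits the child, the inclusion list admits the child, and the sample size paragraph counts the child among the 50. The exclusion list, read literally, removes the child. The logical complement of positive on either test is negative on both, and the exclusion list does not say that.

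**The case against.** The study calls itself descriptive, and load is reported at every visit. A child positive for a whole year would be seen and would contradict the stated hypothesis, whatever the means show. That stands. A reader might infer that persistent carriage is analysed away; the documents do not support this. The protocol is silent on uncleared children and nowhere says they are dropped. The weakness lies in the comparison of means, not in every output.

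The clearance wording can be read as naming the test (PCR rather than culture) and not as saying that one negative ends carriage. A child with a false negative also stays under monthly sampling, so a later positive would be recorded. Both points are fair, but 12.1.6 does not say how a later positive alters the time to clear, so the wording still needs alignment.

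The sizes above rest on assumptions. Two specimens are taken per visit, which may raise detection. Misses that cluster in the same children would lower the one-negative figures and could raise the two-negative figures. Censoring (part A) and missed detection (part C) also act on the same carriers as alternatives: a carrier with a false negative receives a time that is too short, and one without receives none. The two effects should not be added.

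A reader might also infer that the exclusion wording removes most eligible children, because section 1 calls culture slow and insensitive. No culture-positivity rate is given, so the share cannot be stated, and the surrounding text makes the intended reading plain.

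Calling the study descriptive does not settle the matter. Section 12.1.6 still fixes a comparison of means between groups, and a purely descriptive mean duration has the same bias.

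**Conclusion.** The point holds as a specification fault that should be fixed. A comparison of means is fixed for an outcome that is censored by design, with no rule for children not seen to clear. If they are omitted, duration is understated: about 2.8 to 3.7 months against about 4.3 in the worked scenario. The mean is also blind to the persistent fraction when detection is perfect. The analysis definition of clearance is looser than the follow-up rule, and under independence the difference is large (46% to 86% against 3% to 20% of continuous carriers). The direction of the censoring bias follows from the design; its size depends on assumptions that the protocol does not supply. The exclusion criterion contradicts the inclusion criterion as written. None of the main study's endpoints or Questions 1 to 6 depends on this ancillary analysis, which limits the seriousness.

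**What to change.** In section 12.1.6:

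- Use one clearance definition that matches 12.1.3: the first of two successive visits at which PCR and culture are both negative. State how a single unconfirmed negative at the last visit is treated.
- Censor children who are not seen to clear, whether still positive at the cap or lost earlier.
- Replace the comparison of means with Kaplan-Meier or interval-censored estimates per group, compared by a log-rank test or by the 12-month restricted mean.
- Report the proportion still positive at 12 months per group, with a confidence interval. This addresses the persistence question directly. Keep the visit-by-visit description of load.

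In section 12.1.4, separately, reword the exclusion for both groups as real-time PCR and culture both negative, so that it agrees with the inclusion list, 12.1.3 and the expected 50 children.

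The cost is a change of wording in two sections. No visit, sample or test is added, because the confirming visits are already planned.

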# APPENDIX

## Flowchart FUP study

[figure not shown]

Supplement: Text S1 — Study protocol. (DOC) [file pmed.1001444.s005.doc]
